### Statistical Analyses

Descriptive statistics will be calculated for all variables of interest (eg, knowledge of first aid, stigma, and help-seeking intentions). In order to assess whether randomization results in similar groups, we will examine whether there are differences between the two conditions on relevant covariates (ie, sex, age, educational level, ethnicity, gaming behavior, and depressive symptoms) using *t* tests for the continuous variables and chi-square tests for the categorical variables. Variables that are distributed differently between the two conditions will be entered as control variables in all models testing the effects of the conditions.

We will perform our analyses according to the intention-to-treat principle, meaning we will include all children who filled in the pretest questionnaires in the analyses to test the study hypotheses. We will control for clustered data because children are nested within classes. We will use Mplus version 8 (Muthén & Muthén ) [52] for the analyses, since it has special features to deal with missing data. It also allows for analyzing complex data while controlling for clustering. To test whether children in the experimental condition have shown an increase in mental health literacy and a decrease in stigma at 3- and 6-months follow-up, compared to the control condition, regression analyses will be conducted. Both the effect sizes and the confidence intervals will be reported. Open-ended questions will be analyzed exploratively and indicatively where necessary.

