## Methods

### Design

The effectiveness of Moving Stories will be tested within a randomized controlled trial with two conditions: Moving Stories versus a nonintervention control group (see Figure 1 for the flowchart of the study design). We have chosen not to include a third condition with an alternative program because there is currently no mental health literacy program for young adolescents available in the Netherlands. Classes within a school will be randomized to either condition to avoid skewed distribution of participants over the two conditions due to school effects. The outcomes will be measured by self-report at four assessment points: T1 (pretest, within one week before the start of the program); T2 (posttest, within two weeks after the end of the program); T3 (3-months follow-up); and T4 (6-months follow-up), with the exception of the behavioral outcomes, which will not be assessed during posttest.

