### Procedure

Participants are adolescents in the second year of high school (ie, 12-15 years old). Schools in the Netherlands were approached and asked to participate with at least two second-year classes to allow for within-school randomization. The exclusion criterion was refusal from either the parent or the adolescent to participate.

After schools agreed to participate, the classes were allocated to either the Moving Stories or control condition by an independent researcher using computer-generated random numbers. All parents and adolescents in the participating classes received an information letter via the school with information about the study (see Multimedia Appendix 1). Along with the letter, parents received a consent form, which they had to sign and send back to the researchers in order to give consent for their child’s participation. Before adolescents filled in the pretest, they will also had to give written active consent for participation. All questionnaires at all assessment points were Web based and were either filled in at school or at home.

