### Sample Size

The sample size was based on the expected difference (Cohen *d*=0.40) between the intervention and control condition for mental health literacy and stigma at 3-months follow-up, based on Perry et al [23]. We performed a power analysis using Stata version 14.2 (StataCorp) [49], assuming baseline-adjusted regression analyses (alpha=.05; beta=.20). Our provisional estimates for the correlations between pre- and posttest and between posttest and 3-months follow-up are .50. A coefficient of variation of .19 (estimated mean cluster size=18; estimated cluster size range=11-25 [50]) and an intracluster correlation coefficient of .02 [23] lead to a design effect of 1.35. Taking into account the design effect, we calculated that we need 3.75 classes per condition to show the expected effect, rounding up to four classes per condition, with 18 adolescents per class. To adjust for a *t* distribution [51], we added one class per condition, resulting in five classes (ie, 90 adolescents) per condition and a total necessary sample size of 180. Since we will perform the analyses according to the intention-to-treat principle, dropout was not taken into account.

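### Control variables are selected by pupil-level baseline significance tests in a class-randomised trial, and the listed candidates leave out the pretest outcome score that the sample size relies on

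*Protocol article*

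**What the plan says.** Under Design, the unit of allocation is the class: "Classes within a school will be randomized to either condition". Under Procedure, allocation was done "by an independent researcher using computer-generated random numbers", and the account then turns to information letters and consent.

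Under Statistical Analyses, the two conditions are compared on "sex, age, educational level, ethnicity, gaming behavior, and depressive symptoms", using t "tests for the continuous variables and chi-square tests for the categorical variables". The consequence is fixed: "Variables that are distributed differently between the two conditions will be entered as control variables in all models testing the effects of the conditions". No threshold for a difference is given. The next paragraph, on the tests of the study hypotheses, adds: "We will control for clustered data because children are nested within classes".

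Under Sample Size, the power calculation was done "assuming baseline-adjusted regression analyses", with provisional correlations of .50 between successive measurements.

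**The concern.** Three features of the rule look wrong.

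- **Selection criterion.** Whether a covariate is worth adjusting for depends on how well it predicts the outcome. The rule uses only its imbalance at baseline. A strong predictor that happens to balance is left out, and an irrelevant variable that happens not to balance goes into every model.
- **Unit of analysis.** The named tests treat pupils as independent, but ten classes were allocated. The only sentence on clustering belongs to the hypothesis tests, and nothing extends it to the baseline comparison.
- **T1 score.** The pretest value of the outcome is not among the six candidates, and the regression in the same section does not name it. The sample size depends on adjusting for it.

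At stake are the precision of a trial with five classes per condition and a primary model that is not known until the baseline data are in.

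**Working it through.** **1. The protocol's own figures.** Inputs from Sample Size: d = 0.40, alpha .05 (two-sided assumed), power .80, correlations .50, mean class size m = 18, coefficient of variation (CV) .19, ICC .02.

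- Design effect = 1 + ((CV² + 1)m − 1) × ICC = 1 + (1.0361 × 18 − 1) × .02 = 1.353. The stated 1.35 is reproduced.
- Unadjusted n per condition = 2(1.96 + 0.84)²/0.40² = 98.1.
- Baseline adjustment with the mean of two post measures has variance factor (1 + .5)/2 − .5² = .50. This gives 50 per condition; 50 × 1.35 = 67.5; 67.5/18 = 3.75 classes. The stated 3.75 is reproduced.
- Without the baseline term, but still averaging two post measures, the factor is (1 + .5)/2 = .75. This gives 74 per condition; 74 × 1.35/18 = 5.55 classes.

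So the stated 3.75 classes depends on adjusting for the T1 score.

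**2. Size of the baseline tests.** A nominal 5% test that ignores clustering has true size 2(1 − Φ(1.96/√DE)), where DE is the design effect at the covariate's ICC. The protocol gives no covariate ICC and no threshold, so both are assumptions (.05 two-sided).

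| Covariate ICC | DE | True size | At least one of six flagged |
|---|---|---|---|
| 0 | 1.000 | .050 | .265 |
| .02 | 1.353 | .092 | .44 |
| .05 | 1.882 | .153 | .63 |
| .10 | 2.765 | .239 | .81 |

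The last column is 1 − (1 − size)⁶ and assumes independent tests. Simulation with ten classes of 11 to 25 pupils gave .098 at ICC .02 and .239 at ICC .10.

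**3. Effect of randomising within schools.** The table places all clustering at class level. With schools of 2, 2, 2 and 4 classes, split evenly (assumption), the size changes as follows in simulation:

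| Share of clustering between schools | ICC .02 | ICC .05 | ICC .10 |
|---|---|---|---|
| Half | about 7% | 10–11% | 15–16% |
| 80% | about 6% | 6–7% | about 8% |

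**4. Precision.** Simulated null trials with one pupil-level covariate (covariate and outcome ICC .02) gave these standard deviations of the effect estimate:

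| Correlation with outcome | Never adjusted | Under the rule | Always adjusted |
|---|---|---|---|
| .5 | .1718 | .1634 | .1497 |
| .3 | .1732 | .1704 | .1669 |

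The variance under the rule, relative to always adjusting, is (.1634/.1497)² = 1.19 at correlation .5 and (.1704/.1669)² = 1.04 at .3. Never adjusting for a covariate correlated .5 costs (.1718/.1497)² = 1.32. That last figure is the relevant one if the T1 score is left out.

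**5. Type I error.** In the same simulation at correlation .5, with a cluster-robust t test on 8 degrees of freedom, rejection was .054 under the rule, .066 always adjusted and .064 never adjusted. Selection did not inflate it.

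Class-level binary covariates behave differently. With zero, one and two such candidates under the chi-square rule, rejection was about 12%, 17–18% and 21–22% for an uncorrected sandwich with a normal reference. With a small-sample scaling and t(8) it was about 6.5%, 10–11% and 14–15%. Always entering them inflates it similarly (18% and 22–23% with the normal reference), so the cause is class-level terms with ten clusters, not the act of selecting.

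**The case against.** Several points on the other side stand.

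- **The rule is set in advance and uses baseline data only.** It applies to all models alike and leaves no room for an outcome-driven choice. That is true. The model still varies with features of the sample that say nothing about prognosis.
- **Imbalance need not be chance.** Procedure describes allocation before letters and consent, so differential consent could produce real differences. A reader might infer that these tests can detect only chance; the document does not support that. It does not rescue the rule either, because the tests cannot separate the two sources.
- **T1 adjustment may already be intended.** Sample Size says so in terms, and the six variables can be read as additional controls. Likewise, the Depressive Symptoms subsection says that the CDI serves to control for such symptoms, without a balance condition. A reader might infer that T1 adjustment has been dropped; the text does not show that. What remains is that two sections need aligning.
- **Type I error.** A reader might infer that the rule makes the effect tests invalid. For pupil-level covariates the simulations show no such thing. The excess arises only when class-level covariates are added with ten clusters, and the protocol neither says that any candidate is constant within class nor names the variance estimator.
- **Educational level.** If it were constant within class, a split of 36/90 against 54/90 gives chi-square 7.2, p = .007. It is tempting to conclude that any unequal split of classes triggers adjustment. That fails with the expected class sizes of 11 to 25: two classes of 22 against three of 15 give 44/90 against 45/90, p = .88.
- **Clustering in the baseline tests.** That they ignore it is inferred from the tests named and from where the clustering sentence stands; the text does not say so outright.

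**Conclusion.** The point holds as a weakness of a stated rule. Covariates are chosen by tests that carry no information on prognosis and that over-reject when classes are randomised: about 9% instead of 5% at ICC .02, up to about 24% at ICC .10, and close to nominal if most clustering lies between schools. In the one-covariate simulations the rule costs about 4% to 19% in variance compared with always adjusting, for correlations of .3 to .5.

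These figures rest on an assumed threshold of .05, assumed covariate ICCs and, for the six-variable figure, independence. They do not show that the trial's inference is invalid. The change should be made because it is cheap, recovers precision, and brings the analysis into line with the model that the sample size assumes.

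**What to change.** In Statistical Analyses:

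1. Delete the t and chi-square tests as a means of choosing covariates. Report baseline values by arm descriptively.
2. State one covariate set for all effect models, applied regardless of balance and chosen on prognostic grounds: the T1 score of the same outcome where it was measured, T1 CDI, and at most one or two other pupil-level covariates named in advance. Sex is one possibility, although the protocol gives no evidence on its prognostic value.
3. Enter no class-level covariate unless it is named in advance, because only ten classes are available.
4. Say explicitly that this is the baseline-adjusted regression on which Sample Size rests.

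The cost is wording. The variables needed are already collected for outcomes assessed at T1. The fixed set should be recorded before the outcome data are analysed.

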## Results

As of the writing of this paper, four schools and 10 classes have agreed to participate in this study. At pretest, 185 adolescents and their parents gave consent and filled in the first questionnaires. The last of the follow-up data was collected in December 2018.

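### The sample size allows for a t distribution with 10 randomized classes, but the stated analysis has no few-cluster method and no school term

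*Protocol article*

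**What the plan says.** Under Design, the unit of randomization is the class and the stratum is the school: "Classes within a school will be randomized to either condition to avoid skewed distribution of participants over the two conditions due to school effects". Results reports that "four schools and 10 classes have agreed to participate in this study". The Discussion defends allocation within schools on the ground that schools may differ considerably.

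Sample Size arrives at four classes per condition and then allows for a t distribution: "we added one class per condition, resulting in five classes".

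Statistical Analyses names regression in Mplus version 8, with confidence intervals to be reported. On clustering it says "We will control for clustered data because children are nested within classes" and, of the software, "It also allows for analyzing complex data while controlling for clustering". The candidate covariates are sex, age, educational level, ethnicity, gaming behavior and depressive symptoms. School appears neither as a clustering level nor as a covariate or stratum. The section gives no standard-error estimator, reference distribution, degrees of freedom or small-sample correction.

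**The concern.** The two sections treat the same 10 classes differently. The sample size accepts that a comparison of five classes with five cannot use the normal distribution and spends two extra classes on that. The analysis section, from which the p-values and confidence intervals will come, does not carry the allowance forward. Common ways of controlling for clustering rely on many clusters. With 10 they can understate the standard error, and a normal critical value adds to the problem. Intervals would then be too narrow and false positives too frequent.

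School is a separate issue that works in the other direction. Blocking on school removes school differences from the treatment contrast. If the model leaves school out, those differences stay in the estimated error. The test then loses power, and the benefit of the blocking is partly lost.

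**Working it through.** **Inputs from Sample Size:** alpha .05, beta .20, d = 0.40, correlations .50 ("Our provisional estimates for the correlations between pre- and posttest and between posttest and 3-months follow-up are .50"), mean class size 18 (range 11-25, coefficient of variation .19), intracluster correlation .02, design effect 1.35, five classes per condition. **Assumed, because the article does not give them:** a two-sided test, the school correlation (.02 and .05 tried), and the split of classes over schools (2,2,3,3 and 2,2,2,4 tried).

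**1. Reproducing the plan's figure.**
- Unadjusted n per arm: 2 × (1.96 + 0.84)² / 0.40² = 98.1.
- Baseline adjustment with two follow-ups: (1 + r)/2 − r² = 0.75 − 0.25 = 0.50, so 98.1 × 0.50 = 49.06, rounded up to 50.
- Design effect: 1 + [(0.19² + 1) × 18 − 1] × 0.02 = 1.353.
- Classes: 50 × 1.35 / 18 = 3.75, rounded to 4, plus 1 = 5. Total 5 × 18 × 2 = 180.

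The stated figures are reproduced. The factor 0.50 is inferred from that match. The factor for a single follow-up, 1 − r² = 0.75, would give 74 × 1.35 / 18 = 5.55 classes before the t allowance.

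**2. Sandwich with a normal reference, closed form.** Take 5 v 5 equal classes and let S be the within-arm sum of squares of the 10 class means.
- Unbiased variance of the difference: (S/8) × (1/5 + 1/5) = 0.05 S, on 8 df.
- Uncorrected sandwich variance: S/25 = 0.04 S, which is 0.8 of the unbiased value.
- Type I error: P(|t8| > 1.96 × √0.8) = P(|t8| > 1.753) = 11.8%.
- With a C/(C−1) = 10/9 correction the ratio is 0.889, and P(|t8| > 1.848) = 10.2%.

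Simulation with unequal classes and a baseline covariate gave 11.5-12.4% and 10.0-10.6%.

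**3. Random-intercept model with a normal reference** (40,000 runs, 10 classes of 18). Maximum likelihood gives 7.2% at correlation .02, 9.6% at .05 and 4.6% at 0. Restricted maximum likelihood gives 5.8% at .02.

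**4. Schools that differ** (class correlation .02, 8,000 runs per scenario, with a separate check of the sandwich rows):

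| Test | No school variance | School correlation .02 | School correlation .05 |
|---|---|---|---|
| Uncorrected sandwich, z, school omitted | about 12% | 8.9-10.7% | 6.4-7.7% |
| Class-level t, 8 df, school omitted | 4.4-5.3% | 3.3-4.1% | 2.2-2.6% |

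Two further results hold across all scenarios. School dummies combined with an uncorrected sandwich z-test give 22-25%. A school-stratified class-level t test on 10 − 2 − 3 = 5 df gives 4.4-5.5%.

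**5. Power of the t-based tests.** With the plan's factor, SE = √(0.50 × 1.35 × 2/90) = 0.1225, and 0.40/0.1225 = 3.27. Power is 81.5% with t on 8 df, and 74.3% with t on 5 df if school terms explain no variance.

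**The case against.** The strongest reply is that the article never says sandwich errors or z-tests. Reading them into its wording means assuming a software setting. Estimator, degrees of freedom and handling of the stratum are often left to an analysis plan, and none is shown here. The authors plainly knew of the few-cluster problem, since they sized for it. The two parts of the concern also do not add up: 12% needs school variance near zero, whereas omitting school matters only when schools differ, and the Discussion expects that they may.

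Most of this stands, and it rules out three stronger readings that a reader might infer.
- That the plan's false-positive rate is 12% on every outcome. The estimator is not stated, 12% is the top of the range, and only a continuous outcome was examined. Symptom recognition is scored correct or not, and the behavior items apply to a subgroup.
- That the plan decided to discard the school blocking. The text is silent on school; it does not exclude it.
- That omitting school adds to the inflation. It reduces it.

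What the reply does not remove is the mismatch within the article. The analysis section goes beyond leaving detail open: it names the software, the model and the clustering level, and promises intervals from them. At the planned correlation and without school variance, every normal-reference route examined exceeds 5%, although restricted maximum likelihood does so only slightly.

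**Conclusion.** The point holds as an inconsistency between the sizing and the stated analysis. It is not a demonstrated error rate. If tests use a normal reference, type I error for a continuous outcome is about 7-12% at the planned correlation when schools do not differ; the three cases are about 7%, 10% and 12%. If schools differ and are left out, the sandwich figure falls to about 9-11% or 6-8% at the two assumed school correlations. A class-level t test on 8 df, otherwise valid, then becomes conservative at about 3-4% or 2-3%.

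Confidence is high for the mismatch and for the closed-form figures. It is lower for which figure applies, because that depends on an unstated estimator and an unknown school variance. If a fuller analysis plan already specifies a few-cluster method and the role of school, citing it resolves the point.

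**What to change.** Keep the individual-level baseline adjustment, but take the tests and confidence intervals from a method suited to 10 clusters with a t reference. One option is a two-stage analysis of covariate-adjusted class means, which held its level in the checks. Another is a mixed model with small-sample degrees of freedom. Kenward-Roger was not simulated, and restricted maximum likelihood with t on a fixed 8 df was conservative at correlation .02 (2.9%).

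Prespecify whether school enters as the randomization stratum. Decide the two changes together: school terms should not be added to an uncorrected sandwich z-test, where error reaches 22-25%.

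The cost is analysis-plan wording and one further model, with no new data. Intervals widen: the critical value rises from 1.96 to 2.31 on 8 df (2.31/1.96 = 1.18) or 2.57 on 5 df (2.57/1.96 = 1.31). Power stays near the planned 80% on 8 df (about 81%) but drops to about 74% on 5 df if school explains nothing. School variance that the stratum removes would offset some of that loss. Both power figures rest on the 0.50 variance factor; with 0.75 they would be about 65% and 57%.

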**Objective:**

Our aim is to describe the protocol for a study that will test the effectiveness of the program Moving Stories in a Dutch adolescent sample. We hypothesize that adolescents who participate in the program Moving Stories will have better mental health literacy and less stigma regarding depression compared to adolescents in the nonintervention control group at posttest and at 3- and 6-months follow-up. We also expect a positive change in actual help-seeking and first aid behavior at 3- and 6-months follow-up.

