### Objectives

The goal of this paper is to describe the protocol for a study that will test the effectiveness of the program Moving Stories in a Dutch adolescent sample by means of a randomized controlled trial. Our first hypothesis is that adolescents who participate in the Moving Stories program will have better mental health literacy and will endorse fewer stigmatizing attitudes regarding depression than adolescents who do not participate, both directly at posttest and at 3- and 6-months follow-up. Second, we expect a change in help-seeking and first aid behavior. At 3- and 6-months follow-up, we expect that adolescents in the Moving Stories group, compared to the control group, will have sought more help if they were experiencing depressive symptoms or provided increased appropriate first aid if they were in contact with a peer who was experiencing depressive symptoms.

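### Hypothesis 1 covers posttest but the stated effect analysis names only 3 and 6 months; separately, the sample size appears to rest on two averaged follow-ups although its stated target is 3 months alone

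*Protocol article*

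**What the plan says.** **Hypothesis.** In the protocol article, Objectives expects the literacy and stigma differences "both directly at posttest and at 3- and 6-months follow-up". The Abstract's Objective agrees: "compared to adolescents in the nonintervention control group at posttest and at 3- and 6-months follow-up".

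**Measurement.** Design lists "T2 (posttest, within two weeks after the end of the program" among four assessment points, "with the exception of the behavioral outcomes, which will not be assessed during posttest". Literacy and stigma are therefore collected at T2.

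**Analysis.** Statistical Analyses has one sentence on the effect analysis. It announces regression analyses to test for "an increase in mental health literacy and a decrease in stigma at 3- and 6-months follow-up", and posttest is not in it. The section adds that clustering within classes will be controlled for in Mplus. It does not say whether the two time points are analysed separately or jointly.

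**Sample size.** The calculation rests on the "expected difference (Cohen *d*=0.40) between the intervention and control condition" "for mental health literacy and stigma at 3-months follow-up", with baseline-adjusted regression, alpha .05 and beta .20. The provisional "correlations between pre- and posttest and between posttest and 3-months follow-up are .50". No pretest-to-3-month correlation and no 6-month correlation is given. The result is 3.75 classes per condition, rounded up to four, plus one for the t distribution: five classes of 18 per condition, 180 in total.

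**The concern.** Two separate things do not line up.

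First, the list of time points in the analysis is shorter than the list in the hypothesis, for outcomes that are measured at every one of them. Followed literally, the plan leaves the immediate effect of the program without a test. A posttest result could then be reported or left out after the data are seen, and either choice would agree with some part of the article.

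Second, a baseline-adjusted comparison at 3 months depends on the correlation between pretest and 3 months. Sample Size does not give that one. It gives the two correlations that would be needed if posttest and 3 months were combined. If the 180 was obtained for an average of two follow-ups, the 80% power does not automatically carry over to the 3-month difference that the section names as its target.

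**Working it through.** **Part 1: time points side by side (literacy and stigma)**

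| Place | T2 | T3 | T4 |
|---|---|---|---|
| Abstract, Objective | yes | yes | yes |
| Objectives, hypothesis 1 | yes | yes | yes |
| Design, measured | yes | yes | yes |
| Statistical Analyses, effect sentence | **no** | yes | yes |

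T3 and T4 alone is the right schedule for hypothesis 2 (behavior, not assessed at T2), but the sentence applies it to literacy and stigma.

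**Part 2: what the sample size rests on**

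Inputs from Sample Size: d = .40, alpha = .05 (taken as two-sided; sidedness is not stated), power .80, correlations .50, mean class size 18, coefficient of variation .19, intracluster correlation .02.

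1. Design effect: 1 + ((.19² + 1) × 18 − 1) × .02 = 1.353, matching the stated 1.35.
2. Unadjusted n per condition: 2 × (1.96 + .842)² / .40² = 98.1.
3. Variance factor with one baseline and p averaged follow-ups, r1 being the correlation between follow-ups and r01 that of each follow-up with baseline: (1 + (p − 1) × r1)/p − r01².
4. Reproducing the plan's figure, p = 2, all correlations .50: factor (1 + .50)/2 − .25 = .50. Then 98.1 × .50 = 49.06, rounded up to 50, and 50 × 1.35 / 18 = **3.75 classes**. Rounding to 4 and adding 1 gives 5 per condition, 180 in total. This is an exact match.
5. Single 3-month follow-up, p = 1, pretest-to-3-month correlation *assumed* .50: factor 1 − .25 = .75. Then 98.1 × .75 = 73.6, rounded up to 74, and 74 × 1.35 / 18 = **5.55 classes**. The article's own rounding and added class give 7 per condition, 2 × 7 × 18 = 252 in total.
6. Other variants do not give 3.75: single follow-up one-sided 4.35; two follow-ups one-sided 2.93; three follow-ups two-sided 3.08; no baseline adjustment 7.43; 3 months adjusted for both pretest and posttest 4.95 (two-sided) or 3.90 (one-sided).

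**Power at five classes of 18 per condition.** Standard error = √(factor × 1.353 × 2/90); t with 2 × 5 − 2 = 8 df.

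| Contrast | Factor | Power, t (8 df) | Power, normal |
|---|---|---|---|
| T2 and T3 averaged, all r = .50 | .50 | .81 | .90 |
| T3 alone, r = .30 | .91 | .57 | .68 |
| T3 alone, r = .50 | .75 | .65 | .76 |
| T3 alone, r = .70 | .51 | .81 | .90 |

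In the T3-alone rows, r is the assumed pretest-to-3-month correlation. The averaged contrast needs it too: at r = .30 the factor is .75 − ((.50 + .30)/2)² = .59 and t-based power falls to about .75.

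**The case against.** On part 1, a reader might infer that the investigators decided to drop the posttest comparison. The document does not support that. It nowhere says posttest will not be analysed. Statistical Analyses speaks of testing the study hypotheses in general, and its effect sentence also leaves out the behavioral outcomes of hypothesis 2, so it is not an exhaustive list. An omitted word is the likelier explanation, and a fuller plan may include the test. This lowers the gravity but does not close the gap: the general phrase defines who is analysed, and the one sentence that names time points disagrees with the hypothesis.

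On part 2, three stronger readings are tempting.

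- *That the sample size demonstrably uses posttest.* The number of follow-ups is never stated; the .50 factor is worked back from 3.75. A joint model of T3 and T4 with the same correlations would also give 3.75. The listed correlations, none of them at 6 months, make T2 and T3 the more likely pair, but that remains an inference.
- *That separate T3 and T4 regressions are planned and therefore lack power.* The article does not say separate or joint. The power figures for T3 alone apply only if it is tested alone, and they depend on an unstated correlation; near .70 the shortfall disappears.
- *That a longitudinal model with an arm-by-wave term would repair the precision.* With complete data, each wave's contrast in such a model has essentially the precision of a single baseline-adjusted regression. Only an averaged contrast has the .50 factor, and no stated hypothesis concerns an average.

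**Conclusion.** Part 1 holds on the text alone: literacy and stigma at posttest are hypothesised and measured, but no test is stated. It is an inconsistency within the article, not evidence of a decision to leave posttest out.

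Part 2 holds as a qualified statement. The stated 3.75 classes appears to rest on the average of two follow-ups, most likely posttest and 3 months, whereas the declared target is 3 months alone. If 3 months is tested alone with a pretest-to-3-month correlation of .50, power is about .65 (t, 8 df) or .76 (normal) rather than the stated .80. Over correlations of .30 to .70 the t-based figure runs from .57 to .81. These values assume a two-sided test, the stated design effect and no dropout. The two parts are independent: adding a posttest test settles the first and does nothing for the second.

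**What to change.** 1. In Statistical Analyses, add posttest to the 3- and 6-month time points for the literacy and stigma outcomes, using the same baseline-adjusted, class-clustered analysis. Keep T3 and T4 only for the behavioral outcomes.
2. In Sample Size, state which follow-ups the formula averaged and the pretest-to-3-month correlation assumed. Then either restate the power for the single 3-month contrast, with a range over that correlation, or say that the 80% applies only to the averaged contrast.
3. Optional: report an averaged T2–T3 contrast from a joint model. If it is added, label it as additional, since no hypothesis names it and follow-up collection ended in December 2018.

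The first two changes cost wording and a short recalculation, and need no new data. The sample can no longer be enlarged, so the second changes how a null 3-month result is read, not the design. The optional contrast requires a joint model that the article does not currently specify.
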